## Abstract

**Background:**

High-intensity repetitive task-specific practice might be the most effective strategy to promote motor recovery after stroke, and electromechanical-assisted gait training represents one of the treatment options. However, there is still difficulty in clarifying the difference between conventional gait training and electromechanically assisted gait training.

**Methods:**

The study is a multicenter, randomized, parallel-group clinical trial for stroke patients. Three clinical research centers in Korea (Dongguk University Ilsan Hospital, Chungnam National University Hospital, and Seoul National University Bundang Hospital) will participate in the clinical trial and 144 stroke patients will be registered. Enrolled patients are assigned to two groups, an experimental group and a control group, according to a randomization table. In addition, patients are treated for half an hour (one session) five times a week for 4 weeks. Both groups carry out basic rehabilitation (central nervous system development therapy and strength exercise) and the experimental group executes robotic walking rehabilitation treatment, and the control group executes conventional gait rehabilitation treatment. The primary endpoint variable is the Functional Ambulation Category (FAC) that determines the degree of independent walking and is measured before, after, and after 4 weeks of treatment. Secondary endpoint variables are 11 variables that take into account motor function and range, measured at the same time as the primary endpoint variable.

**Discussion:**

There are still insufficient data on the effectiveness of electromechanical-assisted gait training for stroke patients and large-scale research is lacking. Thus, the research described here is a large-scale study of stroke patients that can supplement the limitations mentioned in other previous studies. In addition, the clinical studies described here include physical epidemiological analysis parameters that can determine walking ability. The results of this study can lead to prove the generalizable effectiveness and safety of electromechanical-assisted gait training with EXOWALK®.

**Trial registration:**

Clinical Research Information Service (CRIS), Republic of Korea KCT0003411, Registered on 30 October 2018

**Supplementary Information:**

The online version contains supplementary material available at 10.1186/s13063-022-06660-8.

## Background

Gait training following a stroke has the potential benefits to increase walking speed as a result of training results in similar improvements in walking quality and economy [1]. For gait rehabilitation, highly repetitive practice restores gait function [2]. A number of rehabilitation robots consisting of treadmill and exoskeleton have been developed to assist people with brain lesions in walking training, mainly in Europe and the USA, and some have been commercialized. Automated electromechanical gait training devices were developed to reduce dependence on therapists [3].

Electromechanical-assisted gait training that requires repetitive tasks can improve the neuro-plasticity with motor learning focus on the reorganization of brain tissue, resulting in better balance and faster gait speed [4]. Seven papers concluded that the group that received the walking rehabilitation robot treatment in the 2017 Cochran review was more effective than the group that received the conventional gait rehabilitation treatment, and six papers did not [5]. Many of evidence suggests that high-intensity repetitive task-specific practice might be the most effective strategy to promote motor recovery after stroke, and therefore, electromechanical-assisted gait training represents one of the treatment options [6]. The previous study of this device revealed that electromechanically assisted gait training for 30 min each day for 5 days a week for a period of 4 weeks was as effective as gait training by a physical therapist [7]. A recent study reported the effectiveness on gait function of electromechanically assisted gait training with chronic stroke patients [8].

Conventional gait training conducted by a physical therapist was a standard method of gait training for stroke patients. After the introduction of robot rehabilitation, many studies investigated the effectiveness of electromechanically assisted gait training by comparing it with that of conventional gait training [5]. However, many studies still have difficulty to clarify the difference between conventional gait training and electromechanically assisted gait training and besides presented one of the reasons for the limitation of insufficient participants [9–11]. Now we need to conduct a large-scale randomized design to determine the effectiveness of electromechanical-assisted gait training by comparing it with physical therapist-assisted conventional gait training.

EXOWALK® (HMH Co., HR-01, A67020.02, Grade 2, South Korea) is a recently developed electromechanical exoskeleton-assisted gait training device. This design provides a stable and firm standing ability with little chance of falling and obviates the need for an additional cane or walker compared with currently popular exoskeletons. Such designs are user-friendly without the need for a harness for weight support. Clinical data on the validity and safety of this technology needs to explore this new market. Accordingly, in order to establish clinical efficacy and safety grounds for health insurance registration of new medical technology certification and rehabilitation robot therapy, clinical trials for proving the safety and effectiveness of walking rehabilitation of the new medical device EXOWALK® are conducted for stroke patients with walking disabilities.

We have estimated the sample size by setting the change of gait function more conservatively and conduct a multi-center, large-scale randomized design to determine the effectiveness of electromechanical-assisted gait training with the EXOWALK®.

## Method/design

### Study design

This study on the efficacy and safety of electromechanical-assisted gait trainer EXOWALK ® (HR-01) is a multicenter, randomized, superiority, and parallel-group study with a 1:1 allocation ratio. All enrolled participants are patients with stroke. Three clinical research centers in Korea participate in this trial: Dongguk University Ilsan Hospital, Chungnam National University Hospital, and Seoul National University Bundang Hospital. The 144 participants who met the inclusion criteria were assigned 72 each to the test and control groups. If the study protocol is changed, the changes and reasons are delivered by e-mail to the research participating organizations. The changed research protocol is submitted to the IRB for deliberation.

A strategy to achieve adequate participant registration is to promote the installation of posters and hand-outs in hospitals for patients and visitors to view. Each participant provides informed consent before enrollment. The research director explains the contents of the consent form to the patient for 30 min using terms that are easy for the general public to understand. We identify the schedule of the participants and schedule a visitable date to prevent participants from dropping out and complete the follow-up. Also, when the date of the visit approaches, we inform the participants in advance.

### Screening

The screening is conducted based on data from patients who agreed in the agreement, patients who met the inclusion and exclusion criteria, and hospitals. The target sample size is 144 participants. The eligibility assessment was conducted by a rehabilitation doctor according to inclusion and exclusion criteria. The patients were included within 1 week after eligibility assessment.

### Inclusion/exclusion

The patients are screened for a stroke, 10 or more Mini-Mental State Examination (MMSE), Modified Ashworth Scale (MAS) grade 2 or lower, and standing with an assist. The following patients are excluded: (1) patients with poor cognition that are difficult to carry out instructions; (2) ataxia; (3) patients with MAS grade 3 or above; (4) patients with severe leg arthritis; (5) difficulty walking due to joint swelling of the lower leg; and (6) situations where other walking training cannot be performed.

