### Outcome measurements

In this study, the demographic and clinical characteristics of the participants are measured and documented after screening. Demographic information record gender, date of birth, height, weight, and joint problems or not. And clinical characteristics record a total of five screening criteria. Screening criteria are the name of the diagnosis, cause of the disabilities (brain infarction, cerebral hemorrhage), the paralysis side (Rt., Lt., both, quadriplegia), the possibility of expression of intention (standard: MMSE 10 or higher), and the lower limb spasticity MAS score (standard: MAS grade 2 or lower).

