#### Primary outcome

The Functional Ambulation Category (FAC) is the primary endpoint for determining the existence of independent walking through a concise level assessment. Primary endpoints are evaluated once in the baseline (pre-treatment), 4 weeks after the baseline (post-treatment), and 4 weeks after the last treatment (follow-up), a total of three assessments (Table 1). FAC is a variable that was evaluated by dividing by 1 to 6 depending on the degree of need for assistance when walking, and FAC accounts for more than 55% as a result of the validity evaluation of the research paper on the rehabilitation robot in the 2017 Cochrane review. FAC level ranges from level 1 in “Nonfunctional” to level 6 in “Independent Level and Non-Level Surfaces.”

**Table 1 Tab1:** Content of outcome measurement

Treatment number							
Outcome measure	Pre	1w	2w	3w	4w	Post	F/U
Primary outcome							
FAC	X					X	X
Secondary outcomes							
RMI	X					X	X
Walking velocity	X					X	X
Waking capacity	X					X	X
MI	X					X	X
Berg Balance Scale	X					X	X
MBI	X					X	X
Step counting	X					X	X
Borg scale	X					X	X
Swing time asymmetry	X					X	X
Step length asymmetry	X					X	X
Propulsion asymmetry	X					X	X

*Pre* pre-treatment, *1w* five times per week for the first week, *2w* five times per week for the 2nd week, *3w* five times per week for the 3rd week, *4w* five times per week for the 4th week, *Post* post-treatment, *F*/*U* follow-up, *FAC* Functional Ambulation Category, *RMI* Rivermead Mobility Index, *MI* Motricity Index, *MBI* Korean version of the Modified Barthel Index

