### Sample size

The primary endpoint is the FAC difference before and after training. Data were available on this parameter from a previous trial (Hiroko Watanabe et al. 2014). Hiroko Watanabe et al. show a study on the improvement of stroke walking ability using the hybrid assisted limb (HAL), a representative device of the walking rehabilitation robot. According to the reference, the mean change in existing medical devices was 0.54 and 1 in the test group and HAL group. The newly developed medical device for use in this study was expected to produce about 25% better results in performance than in the HAL group, assuming a variation of 1.25. Therefore, it was assumed that the difference between the variation in the FAC of the test medical device and the comparator device was 0.71 and that the standard deviation was conservatively approached to assume the largest value of 1.4. Two-sided tests were used for sample size estimation. The number of participants per group to achieve overall power of 80% under the significant level of 0.05 is 65. To allow for a possible 10% dropout rate, 144 people were registered per group with 72 people.

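### The entry criteria set no explicit upper limit on walking ability, so patients already at the top FAC level could be enrolled and would weaken the primary comparison

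*Protocol article*

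**What the plan says.** All references are to the protocol article.

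- **Objective (Background).** The trials of the device "are conducted for stroke patients with walking disabilities".
- **Inclusion (Inclusion/exclusion).** Patients need a stroke, an MMSE of at least 10, and "Modified Ashworth Scale (MAS) grade 2 or lower, and standing with an assist".
- **Exclusion (same section).** The first four items are poor cognition, ataxia, MAS grade 3 or above and severe leg arthritis. The last two are "difficulty walking due to joint swelling of the lower leg; and (6) situations where other walking training cannot be performed".
- **Screening record (Outcome measurements).** The "clinical characteristics record a total of five screening criteria": diagnosis, cause, paralysed side, ability to express intention (by MMSE) and lower-limb MAS. None concerns walking.
- **Endpoint (Primary outcome, Sample size).** FAC is "evaluated by dividing by 1 to 6 depending on the degree of need for assistance when walking", and level 6 is "Independent Level and Non-Level Surfaces". The Sample size section defines the primary endpoint as the change in FAC over training.
- **Planned effect (Sample size).** The mean gain is 0.54 with the comparator. For the new device the calculation proceeds by "assuming a variation of 1.25". The difference is 0.71, the SD 1.4, and 65 patients per group are needed for 80% power.

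**The concern.** The objective names people who have trouble walking, but the listed criteria never ask for that. The inclusion items and the exclusions screen out patients who are too impaired or unsuitable, and none screens out a patient who walks well.

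This matters because the endpoint is change on a short, bounded scale. A patient who enters at FAC 6 can stay level or decline but cannot gain. One who enters at FAC 5 can gain one level at most, which is below the mean of 1.25 assumed for the device arm. The sample size makes no visible allowance for either.

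At stake is the chance of showing superiority if the device works as assumed, and whether the result describes the population named in the objective.

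**Working it through.** **1. What the criteria allow.** The phrase about standing with an assist has two readings. As a minimum (the patient can stand, if necessary with help), it sets no upper limit. As a requirement (the patient needs help to stand), it would keep independent walkers out. The first reading fits the rest of the article better, because Table 1 schedules the 10-m and 6-min walk tests for every participant before treatment. On that reading a patient at FAC 6 is eligible as written.

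**2. The plan's own figure.** Inputs from Sample size: difference 0.71, SD 1.4, two-sided 0.05, power 80%.
- Normal approximation: n = 2 × (1.960 + 0.842)² × 1.4² / 0.71² = 61.0, so 62 per group after rounding up.
- Two-sample t-test (noncentral t): 63 per group.
- Normal-approximation n divided by the Wilcoxon efficiency: 62 / 0.955 = 64.9, so 65 per group.
- Dropout: 65 × 1.10 = 71.5, so 72 per group and 144 in total.

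The stated 65 and 144 are reproduced, so the sample-size arithmetic is not at fault. With 65 per arm the t-test has 82% power at 0.71.

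**3. Effect of patients who cannot gain.** The article gives no baseline FAC distribution, so the share p is an assumption, shown over a range. A share p is given zero change in both arms, and the rest follow the plan's means and SD.
- Difference: 0.71 × (1 − p).
- Variance in an arm with mean gain m: (1 − p) × 1.4² + p(1 − p) × m², with m = 1.25 (device) and 0.54 (control). The mixture SD is the square root of the average of the two variances.
- Example, p = 0.20. Difference: 0.71 × 0.80 = 0.568. Device variance: 0.80 × 1.96 + 0.16 × 1.5625 = 1.818. Control variance: 0.80 × 1.96 + 0.16 × 0.2916 = 1.615. SD: √1.716 = 1.31.

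Power is for the two-sided t-test with 65 per arm.

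| Share unable to gain (assumed) | Difference | Power, SD held at 1.4 | Mixture SD | Power, mixture SD |
|---|---|---|---|---|
| 0% | 0.71 | 82% | 1.40 | 82% |
| 5% | 0.67 | 78% | 1.38 | 79% |
| 10% | 0.64 | 73% | 1.36 | 76% |
| 20% | 0.57 | 63% | 1.31 | 69% |
| 30% | 0.50 | 52% | 1.25 | 61% |

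The mixture-SD column is the more coherent one, because patients with no change also reduce the spread. About 5% at the ceiling is enough to bring power just under 80%.

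**4. Patients just below the ceiling.** A simulation drew rounded normal gains with the plan's means and SD and held the final score between 1 and 6. Patients entering at FAC 5 still showed a between-arm difference of about 0.38. They contribute less than the planned 0.71, but not nothing.

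**The case against.** **The wording may already exclude independent walkers.** It can be read as a need for help to stand. The objective and the description of control training, in which the therapist physically assists the patient, both fit an impaired population. This stands in part: the fault is an ambiguous criterion, and the documents do not show that any FAC 6 patient was enrolled. The scheduled baseline walk tests still favour the minimum reading.

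**Dilution may be counted twice.** The gains of 0.54 and 1 come from a cited trial and already average over that trial's own baseline mix. Further dilution arises only if this trial takes in more ceiling patients than that one did. This stands, and the figures depend on it.

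**A broad population is a legitimate choice.** Randomisation balances baseline FAC in expectation. This stands as far as bias is concerned. A reader might infer that the gap biases the comparison between arms. It does not: the cost is a smaller expected difference and lower power.

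**The ceiling effect is easily overstated.** A reader might infer that everyone near the top of the scale adds no treatment contrast, and so ask for a much lower entry cap such as level 4. The FAC 5 result above contradicts the premise, and nothing in the article fixes a cap at that level.

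**The article is a condensation.** The full protocol (version 1.4) is not shown and might word the criterion more tightly. The article also refers subgroup and adjusted analyses to a registry summary, so these cannot be called absent. But it does set out inclusion items, a numbered exclusion list and a stated total of screening criteria, and these do not match its own objective.

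**Conclusion.** The point holds as a mismatch between the stated population and the listed criteria. As written, no explicit rule stops a patient at FAC 6 from entering, and such a patient cannot improve on the primary endpoint.

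The consequence is a possible loss of power whose size cannot be known from the article. Against 82% at 65 per arm, power would be about 78–79%, 73–76%, 63–69% or 52–61% if 5%, 10%, 20% or 30% could not gain. This rests on three assumptions: the shares themselves, a source trial with no such patients, and zero change in both arms for those at the ceiling. A reader might infer that the trial is underpowered. The documents do not support that, because the baseline FAC mix is unreported and may contain few or no patients at level 6.

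**What to change.** **Criterion.** Reconcile Inclusion/exclusion with the objective in Background: say what the standing item means, and state a walking-disability criterion that at minimum excludes baseline FAC 6. FAC is already measured before treatment, so this costs one line and no new assessment, with slightly slower recruitment. Independent walkers would not be covered, but they lie outside the stated objective.

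**This trial.** The Trial status section reports all 144 patients registered, so a new criterion cannot change who was enrolled. What can still be done is to:
- report the baseline FAC distribution by arm;
- adjust the primary FAC comparison for baseline FAC as a fixed choice. The Statistical analysis section selects ANCOVA covariates from baseline homogeneity results for demographic and clinical characteristics, and baseline FAC is not among those it names;
- prespecify, before database lock, a supportive comparison restricted to patients below FAC 6 at baseline. The restriction uses a pre-treatment value, so the comparison remains a randomised one.

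The cost is a short addition to the analysis plan. Adjustment can improve precision but cannot restore a gain that the scale has no room to record, and the restricted comparison has fewer patients, so it should stay supportive.

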#### Secondary outcomes

Secondary endpoints are Rivermead Mobility Index (RMI), 10-m walk test (walking velocity), 6-min walk test (walking capacity), Motricity Index (MI), Berg Balance Scale, the Korean version of the Modified Barthel Index (K-MBI), step counting, Borg scale, swing time asymmetry, step length asymmetry, and propulsion asymmetry. These evaluations are conducted once on the baseline (pre-treatment), 4 weeks after the baseline (post-treatment), and 4 weeks after the last treatment (follow-up), a total of three assessments (Table 1).

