The second endpoints have a total of 11 assessments. First, RMI evaluates motor skills, consisting of 15 questions step by step, depending on the level of bed rotation to running. A total of 15 questions are scored 1 point if yes or 0 if no, and the total sum of the questions is used as a result of the evaluation. Second, walking velocity is a 10-m walk test that measures the speed during 10-m walking, and the unit is meter per second (m/s). Similarly, the third walking capacity is a 6-min walk test that measures the distance that can walk for 6 min, and the unit is meter (m). The fourth MI is an item to be evaluated in a 1 to 99 point system by measuring the lower leg force level from the ankle to the knee. These assessment items consist of three questions, each with a score of 0/9/14/19/25/33 and the total sum of the scores as a result of the evaluation. The fifth Berg Balance Scale is an item that evaluates balance ability by 0 to 56 points. There are 14 questions in total, and each question is scored from 0 to 4 points and the total sum of the scores is used as the result of the evaluation. The sixth K-MBI evaluates the independence of daily activities from 0 to 100 points. This assessment item consisted of 10 questions and, similarly, the total sum of the scores is used as a result of the evaluation. The seventh step counting measures the total number of steps performed by the patient during the specified walk-through time using the same mechanical counter by the three institutes. The measured number of steps is then used as a result of the assessment. The definition of a walk is the number of times a foot touches the ground again. The eighth Borg scale uses Borg’s rating of perceived exertion. Perceived exertion is defined as how much effort it takes to move or exercise. This item evaluates the cognitive level of the subjective effort intensity of the participants in the exercise from 0 (no breathlessness at all) point to 10 (maximal) points. Lastly, the three evaluation items are measured by motion analysis devices. There are swing time asymmetry analyzing gait phase, step length asymmetry analyzing gait phase, and propulsion evaluation item analyzing propulsion.

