### Statistical analysis

Categorical variables such as gender, joint problem disorder, the cause of the disability, and paralysis side in demographic and clinical characteristic information will be presented as *n* (%). The pre-homogeneity will be analyzed by the chi-squared test or Fisher’s exact test. Continuous variables such as age, height, weight, the possibility of expression of intention, and the lower limb spasticity MAS score will be expressed as mean ± standard error (SE) and range. The pre-homogeneity will be analyzed using Student’s *t*-test or Wilcoxon’s rank sum test depending on whether the normality assumption is satisfied.

For all continuous variables of primary and secondary outcomes, the post-treatment measurement results will present the technological statistics, the observed number of patients, mean, SE, and range and compare the differences between groups using Student’s *t*-test or Wilcoxon rank sum test depending on the satisfaction of the normality assumption. The comparison analysis of differences before and after treatment in the group will be conducted using either the paired *t*-test or Wilcoxon’s signed tank test depending on the satisfaction of the normality assumption. In analyzing continuous variables, analysis of covariance (ANCOVA) will be performed after setting the variables as covariates when there are variables that seem to require control in the pre-homogeneity results for demographic and clinical characteristics.

Additional details regarding subgroup and adjusted analyses and definition of analysis populations are available in the clinicaltrials.gov (KCT0003411) in the study summary.

All data will be analyzed using SAS version 9.4 or later. All statistical tests will be two-sided, and the level of significance was set at 0.05.

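### Patients who cannot walk may be enrolled, but the asymmetry comparisons can include only those who step at that visit, and no score for inability is stated for speed or distance

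*Protocol article*

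**What the plan says.** **Eligibility.** In the protocol article, Inclusion/exclusion, the functional requirement is "Modified Ashworth Scale (MAS) grade 2 or lower, and standing with an assist". No minimum FAC level or walking ability is set. The exclusion nearest to the point is "situations where other walking training cannot be performed".

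**Primary scale.** Under Primary outcome, "FAC level ranges from level 1 in “Nonfunctional” to level 6", so the scale has a place for patients who do not walk.

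**Walking outcomes.** Under Secondary outcomes, "walking velocity is a 10-m walk test that measures the speed during 10-m walking" in m/s, and walking capacity is a "6-min walk test that measures the distance that can walk for 6 min", in metres. Three asymmetry measures come from motion analysis devices. Table 1 schedules all five before treatment, after treatment and at follow-up. The article gives no score for a patient who cannot perform a test.

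**Analysis.** Under Statistical analysis, the continuous primary and secondary outcomes are described by "the observed number of patients, mean, SE, and range" among other items. The groups are compared by Student's t-test or the Wilcoxon rank sum test, depending on normality.

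**The concern.** A randomised comparison is protected because membership of the compared groups is fixed before treatment. If a patient counts in a test only when able to step at that visit, membership depends on something the treatment is meant to change. The patients measured in the two arms may then differ for reasons other than the measured outcome.

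The likely direction is unhelpful to the trial. If the device gets more non-walkers walking, and they walk slowly, they enter the experimental arm's average while their counterparts in the control arm are absent from the control average. A real gain in walking could then look smaller on the walking outcomes, or look like a loss. The article's Discussion relies on the walking-analysis parameters to support the claim that robotic therapy is effective for walking, so these outcomes are not incidental.

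**Working it through.** **What the documents fix.** There is no stated figure to reproduce on this point. The sample size (65 per group, 72 after dropout) rests on FAC change alone and is not affected.

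**Step 1: can non-walkers enter?** Assisted standing is enough. The exclusion for situations where other walking training is impossible does not clearly remove them, because under Conventional gait training the therapist guides and walks the patient while assisting. The answer is that they may be enrolled. How many is unknown, because no baseline FAC distribution is given.

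**Step 2: which outcomes lack a value?**
- Asymmetry: none exists without steps. A zero would not serve, since on a difference between sides it would mean perfect symmetry. Motion analysis devices says patients using an assist instrument can be measured over 5–7 m. That helps assisted walkers, not patients who take no steps.
- Speed and distance: zero is a natural score, but the article does not say whether it is used.

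**Step 3: how large could the effect be on speed?** All inputs here are assumptions. Let w0 and w1 be the shares walking under control and device.

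*Scenario A, conversion.* Control walkers average 0.6 m/s. The device adds a share c of patients walking at 0.2 m/s, so w1 = w0 + c, and existing walkers gain g.
- Device mean among walkers: m1 = [w0(0.6 + g) + 0.2c] / w1
- Walkers-only difference: m1 − 0.6
- Difference with non-walkers scored zero: w1·m1 − 0.6·w0

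| Non-walkers under control | c | g (m/s) | m1 | Walkers only | Zero-scored |
|---|---|---|---|---|---|
| 20% | 0.10 | 0.02 | (0.496 + 0.020)/0.90 = 0.573 | −0.027 | 0.516 − 0.480 = +0.036 |
| 20% | 0.10 | 0.05 | (0.520 + 0.020)/0.90 = 0.600 | 0.000 | 0.540 − 0.480 = +0.060 |
| 10% | 0.05 | 0.05 | (0.585 + 0.010)/0.95 = 0.626 | +0.026 | 0.595 − 0.540 = +0.055 |
| 40% | 0.20 | 0 | (0.360 + 0.040)/0.80 = 0.500 | −0.100 | 0.400 − 0.360 = +0.040 |

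Over 10–40% non-walkers, c from 0.05 to 0.20 (never above the non-walking share) and g from 0 to 0.05, the walkers-only difference runs from −0.100 to +0.026 m/s. The zero-scored difference runs from +0.010 to +0.080 m/s.

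*Scenario B, uniform benefit.* Latent ability is normal with SD 0.4 m/s, a patient walks if it exceeds zero, and the device adds 0.1 m/s for everyone. With latent mean μ, the mean among walkers is μ + 0.4·φ(μ/0.4)/Φ(μ/0.4), and the share walking is Φ(μ/0.4).

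| Non-walkers under control | Walkers only | Zero-scored |
|---|---|---|
| 10% | +0.075 | +0.092 |
| 20% | +0.062 | +0.083 |
| 50% | +0.039 | +0.055 |

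Here the benefit is attenuated and never reversed. In both scenarios the walkers-only difference is below the zero-scored one.

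**Step 4: asymmetry.** The article gives no formula or values, so no size is calculated. The selection mechanism is the same, but the amount is unknown.

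**The case against.** The strongest reply is that the article never says non-walkers are dropped. The observed number of patients is one item in a list of descriptive statistics, not a definition of the analysis set. Patients recorded as 0 m or 0 m/s would be observed. The coding of inability may sit in the full protocol, case report form or analysis plan, and Data collection and management refers to data coding and input rules that are not shown. This stands for speed and distance, where the point is conditional.

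It does not answer the point for asymmetry. No coding rule gives an asymmetry to a patient who takes no steps. A worst rank could be assigned, but the test would then mix walking ability with symmetry.

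Four stronger readings are tempting, and the documents do not support them:
- *Non-walkers are in the trial.* Eligibility allows it, but no baseline data show it.
- *The apparent effect will reverse.* Reversal needs conversion of non-walkers with little gain in existing walkers. Under a uniform benefit there is only attenuation.
- *Asymmetry is undefined for bilateral patients.* Outcome measurements records "the paralysis side (Rt., Lt., both, quadriplegia" as categories. The article does not define asymmetry as affected against less affected side, and a left–right difference can be computed for anyone who steps.
- *The main conclusion is at risk.* FAC has a level for non-walkers and is defined for every patient. Five of the eleven secondary outcomes are touched.

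**Conclusion.** The point holds in a limited form. For the three asymmetry measures, the stated between-group comparison necessarily conditions on being able to step at the visit, which treatment may change, if any enrolled patients cannot step. For 10-m speed and 6-min distance the same follows only if patients unable to walk are left blank, and the article is silent on that.

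The size cannot be taken from the documents. On the assumed speed figures it ranges from moderate attenuation (about 0.02 m/s lost from a benefit of 0.06 to 0.09) to a change of sign in some conversion scenarios. If few or no non-walkers were enrolled, the effect is negligible. The primary analysis and the sample size are untouched. It is worth correcting because the correction is cheap and these outcomes are used to support the walking claim.

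**What to change.** 1. State that a patient unable to walk at a visit scores 0 m/s and 0 m, or the worst rank, at every visit. Keep this distinct from a missed visit. FAC is assessed at the same three visits and can be used to check the coding.
2. Compare speed and distance in all randomised patients with the Wilcoxon rank sum test, which the plan already allows, and name it in advance for these two outcomes.
3. Label the three asymmetry comparisons exploratory and restrict them to patients measurable at baseline, so that membership is fixed before treatment.
4. Report, by arm and visit, the number unable to perform each of the five tests.

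The cost is a coding rule and some analysis wording; no new patients or assessments are needed. Recruitment is reported complete, so the rule has to be applied to the existing records, and it should be set before outcomes are compared by arm. The downsides are a spike at zero for speed and distance, which makes mean differences less informative, and fewer patients in the asymmetry comparisons, whose results would then speak only for patients who could already step at baseline.
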